## Abstract

**Background:**

A high proportion of patients with relapsing remitting multiple sclerosis convert to secondary progressive multiple sclerosis (SPMS) characterized by irreversibly progressing disability and cognitive decline. Siponimod (Mayzent), a selective sphingosine-1-phosphate receptor modulator, was recently approved by the European Medicines Agency for the treatment of adult SPMS patients with active disease, as evidenced by relapses or magnetic resonance imaging features of ongoing inflammatory activity. Approval by the Food and Drug Administration covers a broader range of indications, comprising clinically isolated syndrome, relapsing remitting multiple sclerosis, and active SPMS. However, treatment effects of siponimod have not been assessed in a structured setting in clinical routine so far.

**Objective:**

The objectives of AMASIA (imp**A**ct of **M**ayzent [siponimod] on second**A**ry progressive multiple **S**clerosis patients in a long-term non-**I**nterventional study in Germ**A**ny), a prospective noninterventional study, are to assess the long-term effectiveness and safety of siponimod in clinical routine and to evaluate the impact of disease burden on quality of life and socioeconomic conditions. Here, we report the study design of AMASIA.

**Methods:**

Treatment effects of siponimod will be evaluated in 1500 SPMS patients during a 3-year observational phase. According to the genetic polymorphism of CYP2C9, the initial dose will be titrated to the maintenance dose of 1 mg (CYP2C9*1*3 and *2*3) or 2 mg (all other polymorphisms of CYP2C9 except *3*3, which is contraindicated) taken orally once daily. Primary endpoint is the 6-month confirmed disability progression, as assessed by a functional composite endpoint comprising the Expanded Disability Status Scale and symbol digit modalities test to take appropriate account of cognitive changes and increase sensitivity. Further measures including multiple sclerosis activity data; assessments of functional domains; questionnaires addressing the patients’, physicians’, and relatives’ perspectives of disability progression; cognitive worsening; quality of life; and socioeconomic aspects will be documented using the multiple sclerosis documentation system MSDS3D.

**Results:**

AMASIA is being conducted between February 2020 and February 2025 in up to 250 neurological centers in Germany.

**Conclusions:**

AMASIA will complement the pivotal phase III–derived efficacy and safety profile of siponimod with real-world data and will further evaluate several individual treatment aspects such as quality of life and socioeconomic conditions of patients and caregivers. It might help to establish siponimod as a promising option for the treatment of SPMS patients in clinical routine.

**International Registered Report Identifier (IRRID):**

DERR1-10.2196/19598

## Introduction

Most patients with multiple sclerosis (MS), a disabling chronic inflammatory disease of the central nervous system (CNS), initially experience episodes of focal neurological symptoms interspersed by periods of remission (relapsing remitting multiple sclerosis [RRMS]) [1]. Over time, 60% to 90% of RRMS patients convert to secondary progressive multiple sclerosis (SPMS) that is characterized both by an irreversibly increasing disability, with or without new magnetic resonance imaging (MRI) lesions or relapses [1-3], and by the worsening of cognitive function [4]. Cognitive deficits occur more frequently and with higher severity in SPMS patients than in RRMS patients [4].

In individual patients, the risk and timing of the transition from RRMS to SPMS remain largely unpredictable as there are currently no suitable immunologic, clinical, and imaging predictive markers [1,5]. Due to a lack of distinct diagnostic criteria, SPMS is usually diagnosed in retrospect, particularly because pathological parenchymal processes precede clinical symptoms [6,7]. Delineating the clinical profile of RRMS patients at risk of developing SPMS and identifying MRI parameters indicative of SPMS conversion are therefore of primary interest. For this purpose, the real-world evidence study PANGAEA 2.0 [8] has recently been expanded by the additional EVOLUTION study arms [9]. The long-term objective of PANGAEA2.0 EVOLUTION is to establish more accurate and unified diagnostic criteria for the detection of SPMS [10].

As with diagnosis, treatment options for SPMS are limited. Disease-modifying therapies indicated for RRMS as well as investigational RRMS treatments have failed to prevent or slow down disability progression in progressive MS in general [11] and, in particular, in SPMS [5,12-15]. The European Medicines Agency (EMA) has approved only interferon β-1b specifically for SPMS with superimposed relapses [13]. Until now, no immunomodulatory and immunosuppressive drugs have been available for the treatment of SPMS patients without superimposed relapses [16,17]. Siponimod (Mayzent) was approved by the EMA in 2020 for the treatment of adult SPMS patients with active disease, as evidenced by relapses or MRI features of inflammatory activity, commonly interpreted as gadolinium (Gd)-enhancing T1 lesions or active, new, or enlarging T2 lesions [18]. In 2019, the Food and Drug Administration had already approved siponimod with a broader label for the treatment of relapsing forms of MS, including clinically isolated syndrome, relapsing-remitting disease, and active secondary progressive disease, in adults [19].

Siponimod has been developed to selectively modulate the two sphingosine-1-phosphate (S1P) receptor (S1PR) subtypes S1PR1 and S1PR5, which are expressed on lymphocytes (S1PR1), astrocytes, oligodendrocytes, and neurons (S1PR1 and S1PR5) [20]. S1P interaction with S1PR1 expressed on autoreactive lymphocytes appears to be a major driver in early MS pathogenesis, because this interaction is essential for the egression of these cells from secondary lymphoid organs and their infiltration into the CNS [21]. Compared to RRMS, peripheral inflammatory infiltration plays a smaller role in SPMS, as reflected by a low frequency of new Gd-enhancing lesions. Instead, neurodegeneration driven by CNS-intrinsic inflammation is regarded as the predominant feature leading to progressive brain volume loss. Preclinical studies have identified direct neuroprotective properties of siponimod mediated through S1PR1 and S1PR5 receptors (ie, the prevention of synaptic degeneration and promotion of CNS remyelination) [22-24]. In this respect, siponimod represents an improvement over fingolimod (Gilenya), an oral S1P analogue targeting all 5 S1P receptors except S1PR2, for use in patients with highly active or rapidly evolving, severe RRMS [25,26]. The higher S1PR-selectivity of siponimod lowers the risk of adverse events (AEs) [27,28], and the shorter elimination half-life [27] allows patients more flexibility (eg, in case of planned pregnancy).

The phase III study EXPAND (EXploring the efficacy and safety of siponimod in PAtients with secoNDary progressive multiple sclerosis; CBAF312A2304) on the efﬁcacy and safety of siponimod in SPMS patients [29] showed three favorable effects of particular importance for SPMS. First, siponimod attenuated inﬂammatory activity in SPMS patients. When compared to placebo-treated patients, more siponimod patients were found free from both Gd-enhancing lesions and new or enlarging T2 lesions. Second, siponimod reduced the risk of disability progression and lowered rates of brain volume decrease indicating that siponimod slows down neurodegeneration. Third, analyses of participants of the EXPAND study revealed significant and clinically meaningful effects of siponimod on cognitive processing speed, as demonstrated by increased scores in the symbol digit modalities test (SDMT) [30]. Compared to placebo, siponimod increased the proportion of patients with sustained SDMT improvement, while the proportion with sustained SDMT deterioration was reduced [31].

By nature, a pivotal study such as EXPAND with limited follow-up and a narrowly defined patient population cannot address the real-world situation of SPMS patients treated by siponimod in clinical routine [32]. We therefore planned AMASIA (imp**A**ct of **M**ayzent [siponimod] on second**A**ry progressive multiple **S**clerosis patients in a long-term non-**I**nterventional study in Germ**A**ny), a noninterventional study (NIS) to assess the treatment effects of siponimod on SPMS patients in clinical routine. While EXPAND included a representative SPMS population with advanced progression, AMASIA focuses on the much narrower EMA label of SPMS with active disease. In addition to long-term clinical effectiveness and safety of siponimod in real-world situations, AMASIA will assess the effects of siponimod on disease progression of SPMS patients by a wide range of clinical and functional tests and questionnaires concerning the patients’, physicians’, and relatives’ perspectives on disability progression and its consequences, including quality of life and socioeconomic aspects [33]. Furthermore, the study design of AMASIA has been developed following the methodology of PANGAEA 2.0 EVOLUTION [9] to enable a propensity score–matched comparison of SPMS patients receiving either siponimod or standard of care. Therefore, on the one hand, AMASIA will assess real-world treatment effects beyond the clinical data obtained by the phase III study EXPAND. On the other hand, it will allow a comparison of real-world treatment effects of siponimod and current standard of care in SPMS patients (Figure 1). With clinical data of the pivotal trial EXPAND as the base, AMASIA aims to analyze the benefit of siponimod treatment for SPMS patients in clinical routine. Results will be set in relation to the matched study PANGAEA 2.0 EVOLUTION, which analyzes patients with SPMS and high risk for SPMS treated by standard of care [8].

In this paper, we report the study protocol of AMASIA, a multicentric, open-label, prospective NIS. The study started in February 2020 and is planned to continue until February 2025. During the 3-year observational phase, data on 1500 SPMS patients treated by siponimod in up to 250 neurological centers in Germany will be documented.

**Figure 1 figure1:**
[figure not shown]
AMASIA within the study framework of siponimod studies. AMASIA: imp**A**ct of **M**ayzent [siponimod] on second**A**ry progressive multiple **S**clerosis patients in a long-term non-**I**nterventional study in Germ**A**ny; EXPAND: EXploring the efficacy and safety of siponimod in PAtients with secoNDary progressive multiple sclerosis [29]; RRMS: relapsing remitting multiple sclerosis; SPMS: secondary progressive multiple sclerosis.

## Methods

### Study Design

AMASIA is a multicentric, open-label, prospective NIS on adult SPMS patients with active disease as evidenced by relapses or MRI features of inflammatory activity. Clinical diagnosis and decision for siponimod therapy will exclusively be made by the treating physician prior to enrollment and according to clinical routine practice and drug label information [34] to ensure real-world conditions.

Both disability progression, as assessed by an increase in Expanded Disability Status Scale (EDSS) scores, and decline of cognitive processing speed are important indicators of disease burden in MS [35-37]. Therefore, in AMASIA, a novel functional composite primary endpoint combining the 6-month confirmed disease progression (6M-CDP) of the EDSS score and SDMT score is utilized. This composite endpoint has been validated in Germany [38] and will be analyzed after 36 months of siponimod therapy to assess long-term effects of siponimod under real-world conditions. This combined 6M-CDP has been successfully applied for the evaluation of EXPAND patients to increase the sensitivity for SPMS progression of both single measures [38,39]. Confirmed disability progression on EDSS is defined as ≥1.0-point worsening in patients with baseline scores ≤5.0 or 0.5-point worsening in patients with baseline scores >5.0. Concomitantly, a ≥4.0-point SDMT worsening from baseline is considered as clinically relevant [40].

To further evaluate the long-term benefits from siponimod treatment in clinical routine, changes in EDSS (after 36 months) and quality of life scores as well as data on safety and long-term adherence (treatment discontinuation and interruption) will be assessed as secondary endpoints. Adherence will be evaluated on the basis of duration of siponimod intake as well as frequency of discontinuation and dose retitration per patient-year. Additional secondary endpoints are exploratory in nature and concern socioeconomic aspects [41], the characteristics of patients receiving their first dose of siponimod, the timing of therapy initiation, and its impact on disease progression. Furthermore, the utility of progression questionnaires (aligned with the online tool MSProDiscuss) and mobile/digital apps for MS monitoring will be documented [42].

Because data are obtained in clinical routine, there is no protocol-defined visit schedule during the 3-year observational phase. However, the most probable frequency of visits in clinical routine is every 6 months after the first visit for dose titration. Basically, functional tests will be performed, and questionnaires will be collected in this interval. These regular visits will be complemented by additional visits to obtain basic parameters on clinical characteristics and MS disease activity every 3 months (Figure 2).

AMASIA will be conducted in accordance with the FSA code (voluntary self-regulation for the pharmaceutical industry [43]); joint recommendations of the German Federal Institute for Drugs and Medical Devices and Paul-Ehrlich-Institute on planning, conducting, and evaluating observational studies [44]; and German Association of Research-Based Pharmaceutical Companies recommendations on improving the quality and transparency of NIS [45]. The guidelines for good pharmacoepidemiology practices [46] as well as the STROBE guidelines for the reporting of observational studies will be applied [47]. Study procedures will be carried out in accordance with the Declaration of Helsinki. The Ethics Committee of TU Dresden (Technische Universität Dresden) approved AMASIA.

**Figure 2 figure2:**
[figure not shown]
Study design of AMASIA (imp**A**ct of **M**ayzent [siponimod] on second**A**ry progressive multiple **S**clerosis patients in a long-term non-**I**nterventional study in Germ**A**ny), a non-interventional study involving an initial dose titration (visit 1), followed by a 3-year observational phase (visits 2-13).

### Study Population

#### Sample Size

We intend to include 1500 SPMS patients in our study. In the EXPAND study [29], 62.2% of siponimod-treated patients had no disease progression, as determined by the combined 6M-CDP assessed using EDSS and SDMT scores (placebo: 52.3%). Since we expect comparable percentages for AMASIA, a total of 1000 patients completing the 36-month observational phase of AMASIA will be sufficient to estimate the combined 6M-CDP with a precision of 3.0%. With an assumed annual dropout rate of 13%, recruitment of 1500 patients will be required to achieve the intended sample size. Likewise, the same sample size is sufficient to assess EDSS changes over 36 months (secondary endpoint). The calculation is based on the assumed annual dropout rate of 13% and assumed standard deviation of 0.6 for EDSS changes from baseline to month 12 and month 24, as observed in EXPAND [29].

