#### Eligibility of Patients

Treatment initiation with siponimod as routine therapy is at the discretion of the treating physician. The decision for siponimod treatment according to drug label information needs to be made before enrollment and independently of study participation. Participants of all genders are eligible if they are 18 years or older, are diagnosed with SPMS, and provide written informed consent. Patients will be excluded due to off-label therapy, pregnancy and breastfeeding, treatment with siponimod before enrollment, and participation in interventional trials or PANGAEA 2.0 EVOLUTION. Patients who do not attend study visits for more than 12 months will exit the study.

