### Statistical Analysis

For analysis, descriptive statistics will be primarily used. The full analysis set includes all patients receiving at least one dose of siponimod with at least one available post-dose data recording. Sample statistics such as median, mean (SD), minimum, maximum, 5% percentile, 1st quartile, 3rd quartile, 95% percentile, and number of valid and missing values will be presented in tabular form. Distributions of absolute and relative frequencies will be reported for nominal and ordinal-level data. Incidence rates of all safety outcomes (events per patient-year) will be evaluated for the patient population included. A propensity score matching adjustment, possibly using a caliper-based nearest-neighbor approach as seen in Alsop et al [66], will be used to compare data from AMASIA with data from the PANGAE 2.0 EVOLUTION arm. Possible predictive baseline and prestudy variables to be included in the model are as follows: age at baseline (years), sex, time since diagnosis at baseline (years), treatment at baseline, number of relapses in the past 12 months before baseline, and EDSS score at baseline. A multivariable logistic regression model will be fitted with the treatment arm as the dependent variable. The distribution of propensity scores before and after matching will be analyzed. Using the Medical Dictionary for Regulatory Activities, AEs are categorized according to system organ class and preferred term for individual adverse events (for AEs, serious AEs, adverse drug reactions, serious adverse drug reactions). For all analyses, SAS version 9.2 will be used.

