AMASIA might provide additional mechanistic information on both the anti-inflammatory effects of siponimod (ie, fewer Gd-enhancing lesions and new or enlarging T2 lesions) and the prevention of neurodegeneration. Traditionally, neurodegeneration during MS pathogenesis is considered to be the consequence of inflammatory attacks mediated by the infiltration of leukocytes in the CNS and the release of inflammatory mediators. However, recent publications suggest that inflammation and neurodegeneration might be two separate aspects in progressive MS, with diffuse white matter injury and cortical demyelination on a background of meningeal, perivascular, and parenchymal inflammation [75]. Indeed, preclinical studies indicated that siponimod prevents and attenuates neurodegeneration [22,76] and promotes remyelination of the CNS [23]. While the EXPAND study indicated that patients with ongoing inﬂammatory activity (ie, superimposed relapses in the 2 years before enrollment) benefited most from siponimod treatment [29], a recent subgroup analysis suggested that treatment effects on disability are largely independent from that on relapses because siponimod reduced the risk for confirmed disability progression in both relapsing and nonrelapsing SPMS patients [77]. AMASIA might confirm these findings with long-term data from clinical routine.

As AMASIA is an observational NIS, it might be associated with some limitations. The lack of randomization to siponimod treatment and the heterogeneity of patients in real-life settings might limit robust conclusions regarding efficacy. However, propensity score–matched comparisons of SPMS patients receiving either siponimod (AMASIA) or standard care (PANGAEA 2.0 EVOLUTION) are thought to assess real-world treatment effects and, therefore, complement phase III data on efficacy. Another limitation to be considered is the potential incompleteness of data obtained during visits not following a predefined visit schedule. Obviously, this risk must be assumed to exist, but the intended systematic, standardized data collection, along with regular monitor visits to ensure data integrity, might be sufficient to minimize bias resulting from incomplete data.

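### The 3.0% precision of the primary endpoint is that of a proportion in 36-month completers, which does not match the stated full analysis set and takes no account of dropout related to progression

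*Protocol article*

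**What the plan says.** Four places in the protocol article bear on the primary combined 6M-CDP.

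- **Sample Size.** The expected rate comes from EXPAND, where "62.2% of siponimod-treated patients had no disease progression, as determined by the combined 6M-CDP assessed using EDSS and SDMT scores (placebo: 52.3" per cent. From this the article concludes that "a total of 1000 patients completing the 36-month observational phase of AMASIA will be sufficient to estimate the combined 6M-CDP with a precision of 3.0" per cent. Dropout enters only as a loss of numbers: "With an assumed annual dropout rate of 13%, recruitment of 1500 patients will be required to achieve the intended sample size".
- **Study Design.** The composite endpoint "will be analyzed after 36 months of siponimod therapy to assess long-term effects of siponimod under real-world conditions". The same section treats stopping the drug as an outcome, since "long-term adherence (treatment discontinuation and interruption) will be assessed as secondary endpoints".
- **Statistical Analysis.** "The full analysis set includes all patients receiving at least one dose of siponimod with at least one available post-dose data recording". The section relies mainly on descriptive statistics, with frequencies for nominal data. It names no time-to-event estimate for the primary endpoint.
- **Eligibility of Patients.** Study exit is tied to attendance: "Patients who do not attend study visits for more than 12 months will exit the study". Stopping siponimod is not given as a reason for exit.

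The Discussion accepts that data may be incomplete and hopes that standardized collection and monitoring "might be sufficient to minimize bias resulting from incomplete data".

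**The concern.** Patients still on siponimod at 36 months, patients still under observation at 36 months, and all dosed patients with one later record are three different groups. The article attaches the primary result to each of them in a different section and does not reconcile them.

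The choice matters because about a third of the cohort is expected to leave. If patients who worsen are more likely to stop or leave, a proportion among those who remain understates progression. A confidence interval built on sampling error alone does not show this. The endpoint also needs six months of confirmation, so a patient who worsens and leaves before confirmation never becomes an event. Monitoring improves the records of patients who attend, but it does not recover the outcomes of those who have left.

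**Working it through.** **Inputs.** From Sample Size: 62.2% without progression (so 37.8% with), 1000 completers, 1500 recruited, 13% dropout per year. The confidence level is not stated. I take 95% two-sided, because 90% would give 2.52% and 99% would give 3.95%. Any link between dropout and progression is my assumption and is varied.

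**1. The plan's own figures.**
- Half-width = 1.96 × √(0.622 × 0.378 / 1000) = 3.005%, as stated.
- Retention = 0.87³ = 0.6585, so the loss is 34.1%.
- 1500 × 0.6585 = 988 completers, with half-width 3.02%. Conversely 1000 / 0.6585 = 1519, against 1500 stated.

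The figures reproduce within rounding. They are those of a simple binomial proportion in completers.

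**2. Gap needed for a 3-point error.** Error of the completer proportion = 0.3415 × (completer rate − dropout rate). It reaches 3.0 points when the gap is 0.03 / 0.3415 = 8.8 points. With completers at 37.8%:

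| Rate in dropouts | Error (points) |
|---|---|
| 37.8% | 0 |
| 40% | −0.8 |
| 45% | −2.5 |
| 50% | −4.2 |
| 60% | −7.6 |

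**3. A dropout mechanism.** Here the true 36-month rate in the whole cohort is set at 37.8%. The progression hazard is h = −ln(0.622)/36 = 0.01319 per month. Dropout has hazard d₀ before progression and m·d₀ after it, with d₀ solved so that overall retention stays at 0.6585.
- Retained without progression: A = exp(−36(h + d₀)).
- Retained after progression: B = ∫₀³⁶ h·exp(−(h + d₀)t)·exp(−m·d₀(36 − t)) dt.
- Completer rate = B / (A + B).

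| m | Completer rate | Error (points) | Gap, dropouts minus completers (points) |
|---|---|---|---|
| 1 | 37.8% | 0 | 0 |
| 1.5 | 35.5% | −2.3 | 6.9 |
| 2 | 33.6% | −4.2 | 12.4 |
| 3 | 30.7% | −7.1 | 20.9 |

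Each error equals 0.3415 times its gap, in agreement with step 2.

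**4. A raw frequency in the full set.** Suppose every early leaver without a recorded event were counted as not progressed. With random dropout at d = −ln(0.87)/12 = 0.01161 per month, the observed proportion is h/(h + d) × (1 − exp(−36(h + d))) = 0.5319 × 0.5904 = 31.4%, which is 6.4 points below 37.8%.

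**5. Precision of a full-set estimate.** For Kaplan-Meier with constant hazards and 1500 patients, the variance is S²/n × h/(h + d) × (exp(36(h + d)) − 1) = 0.622²/1500 × 0.5319 × 1.4414 = 0.0001978. The half-width is 1.96 × √0.0001978 = 2.76%, or about 2.8 points, against 3.0 for completers.

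**The case against.** Planning precision on the expected number of evaluable patients and then inflating for dropout is ordinary practice. The completer count is a sample-size statement, and the only analysis set defined is wider than completers. A reader might infer that the primary analysis discards a third of the cohort and is biased by more than 3.0%. The article does not support that:

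- No section defines a completers-only analysis.
- Sample Size speaks of completing observation, not of completing siponimod. The reference to therapy in Study Design can be read as timing only.
- No progression rate in dropouts is given, and in the 1.5-fold case the error stays below 3 points.
- No rule counts leavers as non-progressors. The planned reporting of valid and missing values points the other way, so the 31.4% illustrates an unstated rule.
- Nothing conditions the siponimod arm on 36 months of persistence in the comparison with EVOLUTION. Selection there would arise only if the Study Design wording were applied literally to that arm alone.

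Censoring and missing-data rules may also stand in a full protocol or SAP that is not shown, and their absence here is no fault.

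All of this stands, and it limits the point. It does not remove the mismatch in what the article does state: the 3.0% belongs to a completer proportion, and neither the on-therapy wording nor the full analysis set describes that group.

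**Conclusion.** The point holds as an inconsistency with a conditional bias. The three descriptions of the primary denominator must be reconciled, and the 3.0% is not the precision of a full-analysis-set result. It covers sampling error only, while 34.1% of patients are expected to be lost.

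The size of any bias depends on an assumed link between dropout and progression. With a true rate of 37.8%, constant hazards and retention of 65.9%, a completer proportion is low by about 2.3, 4.2 or 7.1 points at dropout multipliers of 1.5, 2 or 3. It is low by more than 3 points only if dropouts and completers differ by about 9 points or more. If dropout is unrelated to progression, the completer proportion is unbiased. That 37.8% applies at 36 months is itself the article's expectation, carried over from EXPAND.

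**What to change.** - Make the primary estimate the 36-month cumulative incidence of combined 6M-CDP from siponimod start in the full analysis set. Use Kaplan-Meier, or Aalen-Johansen with death as a competing event. Count events after siponimod is stopped while the patient is still observed, and censor at the last assessment.
- In Study Design, replace the on-therapy timing with *36 months from siponimod start*.
- In Sample Size, restate the precision for this estimator: about 2.8 points with 1500 patients under constant hazards.
- Keep the completer and on-treatment proportions as sensitivity analyses.
- Use the same from-start definition in the comparison with EVOLUTION.
- Add a sensitivity analysis that counts unconfirmed worsening before dropout as an event. Kaplan-Meier still assumes that dropout before a confirmed event is non-informative, including between onset and the 6-month confirmation.

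The cost is a change of wording, standard survival methods and one extra sensitivity analysis, with no added patients. The resulting estimate may look less favourable to siponimod than a completer proportion.

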### Data Collection and Management Using the Multiple Sclerosis Documentation System MSDS3D

Data will be recorded exclusively online by the physician responsible, using the electronic case report form in the MS documentation system MSDS3D [62,63]. The MSDS3D software combines data documentation with patient management. It now has expanded safety management with regard to the characteristics of different treatments and populations [64,65]. Data will be computerized in a pseudonymous form, and all entries will be automatically controlled for plausibility at the time of data entry and reviewed daily by the database coordinator. Data management processes including data analyses will be conducted by the data management team of the responsible clinical research organization (Winicker Norimed GmbH Medical Research).

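### The 3.0% precision stated for the primary endpoint is an independent-patient figure and makes no allowance for clustering in up to 250 centres (minor correction)

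*Protocol article*

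**What the plan says.** The Sample Size section builds its precision statement from three elements. It takes the expected proportion from the pivotal phase III study, where "62.2% of siponimod-treated patients had no disease progression" on the combined EDSS and SDMT endpoint. It sets the number to be analysed as "a total of 1000 patients completing the 36-month observational phase of AMASIA". It concludes that this number "will be sufficient to estimate the combined 6M-CDP with a precision of 3.0" percent. The only inflation described is for dropout: "With an assumed annual dropout rate of 13%, recruitment of 1500 patients will be required to achieve the intended sample size". No confidence level, design effect or intraclass correlation is given.

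Other sections describe how the data arise. The Introduction says that "data on 1500 SPMS patients treated by siponimod in up to 250 neurological centers in Germany will be documented". Study Design and Eligibility of Patients leave the diagnosis and the decision to use siponimod to the treating physician. Study Design also says that the protocol defines no visit schedule, with six-monthly visits the most probable pattern in routine care. Under data collection and management, "Data will be recorded exclusively online by the physician responsible". Statistical Analysis plans mainly descriptive statistics and does not mention centre.

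**The concern.** A binomial half-width of this kind is correct only if patients are independent. Here they come in groups. Patients at one centre share the physicians who decide whom to treat, the local habit of how often patients are seen and tested, and the people who enter the data. The endpoint needs a worsening that is confirmed after six months, so how often a centre measures EDSS and SDMT can affect whether a progression is detected and confirmed. A positive correlation within centres is therefore plausible. If it exists, 1000 completers carry less information than 1000 independent patients.

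Precision is the only statistical property that the article states for its primary endpoint, and it is the justification for the sample size. The figure is printed without the condition under which it holds.

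**Working it through.** **Inputs from the article.** Expected proportion without progression p = 0.622; completers n = 1000; stated precision 3.0%; dropout 13% a year over 3 years; 1500 recruited (all Sample Size). At most 250 centres (Introduction).

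**Inputs assumed.** Two-sided 95% confidence; ICC from 0.01 to 0.10; coefficient of variation (CV) of centre size of 0 or 1; 250 or 100 centres. The article gives none of these beyond the ceiling of 250.

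**Step 1: reproduce the stated figure.** Half-width = 1.96 × √(p(1 − p)/n) = 1.96 × √(0.622 × 0.378/1000) = 3.005 points. At 90% confidence it would be 2.52 and at 99% it would be 3.95, so 95% is the only usual level that fits. Solving for exactly 3.0 points gives n = 1003.5. The stated 1000 therefore leaves no room for a design effect.

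**Step 2: see whether the step to 1500 hides an allowance.** 0.87³ = 0.6585, and 1000/0.6585 = 1519. Conversely, 1500 × 0.6585 = 988 completers, for whom the half-width is 3.02 points. Dropout alone uses up the whole increase.

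**Step 3: add clustering.** With m = 1000/(number of centres), the design effect is DE = 1 + ((1 + CV²) × m − 1) × ICC, and the half-width is 3.005 × √DE.

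- 250 equal centres (m = 4), ICC 0.05: DE = 1 + 3 × 0.05 = 1.15; half-width 3.22; effective sample 1000/1.15 = 870.
- 250 centres with CV 1, ICC 0.05: DE = 1 + 7 × 0.05 = 1.35; half-width 3.49; effective sample 741.
- 100 equal centres (m = 10), ICC 0.05: DE = 1 + 9 × 0.05 = 1.45; half-width 3.62; effective sample 690.

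Half-width in percentage points over the assumed range:

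| Centres | CV of size | ICC 0.01 | ICC 0.02 | ICC 0.05 | ICC 0.10 |
|---|---|---|---|---|---|
| 250 | 0 | 3.05 | 3.09 | 3.22 | 3.43 |
| 250 | 1 | 3.11 | 3.21 | 3.49 | 3.92 |
| 100 | 0 | 3.14 | 3.26 | 3.62 | 4.14 |

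The first row is the most favourable for a given ICC, because 250 is a ceiling and equal recruitment is the best case.

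**The case against.** **The interval method may be in an analysis plan that is not shown.** This is fair. The article fixes no confidence-interval method, and a clustered interval could already be planned. It does not settle the 3.0% printed in the Sample Size section, which assumes independence.

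**The size is assumed and may be close to rounding.** This stands. With 250 equal centres and ICC 0.01 the half-width is 3.05. Figures near 4 points need ICC 0.10 together with very uneven centres or only about 100 of them. The article supports neither condition.

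**Constant rating habits largely cancel.** Progression is worsening from each patient's own baseline, so a centre that always scores high or low contributes little correlation. This argues for the lower end of the ICC range. It does not remove differences between centres in patient selection or in how often patients are tested.

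**The full analysis set is larger than the completers.** If all 1500 contributed, the independent half-width would be 1.96 × √(0.622 × 0.378/1500) = 2.45 points. With 250 equal centres (m = 6) it would be 2.45 × √1.25 = 2.74 at ICC 0.05. That is a best case, and the article does not say how non-completers enter the primary estimate. The stated 3.0% is explicitly tied to 1000 completers, so this does not rescue it.

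**Stronger readings that a reader might infer.** One is that the planned error bar is certainly too narrow. The article specifies no interval and gives no ICC, so this is not established. Another is that the documents say treating physicians assess the endpoint. They say only that the responsible physician records the data; rating by the same person is a reasonable inference, no more. A third is that the standard errors of the comparison with PANGAEA 2.0 EVOLUTION are affected. The matching method is left open, the article does not say whether centres overlap between the two studies, and shared centres could reduce the variance of the contrast. Its direction is unknown.

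**Conclusion.** The point holds as a minor correction. The stated 3.0% is an independent-sample figure, and only dropout was allowed for. For 1000 completers, any positive within-centre correlation makes the true half-width wider, so the direction is clear. The size rests on assumed ICCs and centre sizes. At 250 equal centres the increase is about 0.05 to 0.2 points for ICC 0.01 to 0.05. It is about 0.5 to 0.6 points at ICC 0.05 if centre sizes vary with CV 1 or only 100 equal centres take part. The estimate is descriptive, with no test, margin or success threshold attached, so power and type I error are not involved.

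**What to change.** Keep 1500 patients. Then make two changes.

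1. In the Sample Size section, state that 3.0% assumes independent patients, and give the half-width for a stated ICC range. For ICC 0.02 to 0.05 at 250 centres this is about 3.1 to 3.5 points, depending on how uneven the centres are.
2. Report the primary proportion with a centre-clustered 95% interval, from a cluster-robust variance or a bootstrap of centres. If the analysis plan already provides this, only the first change is needed.

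The cost is one sentence and one analysis option. The downside is a slightly less favourable stated precision. Recruiting more patients to hold 3.0 points is not warranted: at ICC 0.05 with 250 centres of equal size it would take 1003.5 × 1.15 = 1154 completers, or 1154/0.6585 = about 1753 recruits, to recover roughly 0.2 points on a descriptive estimate.
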